### Secondary Estimands

4.2

Secondary outcomes are defined per ICU care episode. ICU length of stay is the time from ICU admission to ICU discharge or death. The durations of invasive mechanical ventilation, noninvasive ventilation, and CRRT are the cumulative hours of each therapy during the ICU episode, as registered in SIR; because death precludes further accrual of these durations, they are analyzed in a time‐to‐event framework with death handled as a competing event. Unplanned ICU readmission is defined, per the SIR definition, as an unplanned return to intensive care within 72 h of ICU discharge, recorded as a binary outcome per discharged episode.

Testing‐intensity outcomes, referred to elsewhere in this protocol as process outcomes, are the number of ABG samples, venous laboratory tests, and chest radiographs per patient‐day.

The environmental outcome—climate impact expressed as carbon dioxide equivalents (CO_2_e, 100‐year global warming potential) attributable to blood gas sampling, laboratory testing, and chest radiography—will be estimated from the process‐outcome counts combined with published and supplier‐derived emission factors per test, with the functional unit being CO_2_e per patient‐day; a separate prespecified analysis plan will detail data sources, system boundaries, and methods, and this outcome is exploratory. Because death precludes the further accrual of tests and of their associated emissions, an intervention that increased early mortality would mechanically appear favorable on both testing intensity and CO_2_e. These outcomes are therefore subordinate to the primary safety outcome: they are interpreted as evidence of benefit only if non‐inferiority for 30‐day mortality is demonstrated, and if it is not, they are reported descriptively with no efficiency or environmental claim made. All such outcomes are expressed per patient‐day as well as per care episode, so that any shortening of the denominator through earlier death remains visible.

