ICU length of stay and the durations of invasive ventilation, noninvasive ventilation, and CRRT are analyzed in a time‐to‐event framework, with time origin at ICU admission (for length of stay) or at initiation of the respective therapy (for therapy durations). The events of interest are, respectively, live ICU discharge and liberation from the therapy; death before the event is treated as a competing event using cause‐specific Cox proportional‐hazards models with a gamma‐distributed cluster‐level frailty to account for clustering, complemented by cause‐specific cumulative incidence functions. Episodes are administratively censored at 30 days from ICU admission for length of stay, and from initiation of the respective therapy for the durations of invasive ventilation, noninvasive ventilation, and CRRT; episodes still ongoing at that point are censored. Treating death as a competing event rather than censoring avoids the bias whereby early deaths masquerade as short, favorable stays. Proportional‐hazards assumptions are assessed with Schoenfeld residuals; where violated, effects are reported as time‐varying or summarized as restricted‐mean‐survival‐time differences. Models are adjusted for the same covariates as the primary analysis. Unplanned ICU readmission within 72 h is analyzed among live ICU discharges with a logistic generalized linear mixed‐effects model specified analogously to the primary analysis.

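### The restricted-mean fallback for ICU stay and therapy durations does not carry over the competing-event handling of death, so it can show extra early deaths as shorter stays or hide them

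*Protocol article*

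**What the plan says.** Section 5.2 of the protocol article sets out the analysis of ICU length of stay and of the durations of invasive ventilation, noninvasive ventilation and CRRT.

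- **Event:** "The events of interest are, respectively, live ICU discharge and liberation from the therapy".
- **Death:** "death before the event is treated as a competing event using cause‐specific Cox proportional‐hazards models", with a cluster-level frailty, "complemented by cause‐specific cumulative incidence functions".
- **Horizon:** "Episodes are administratively censored at 30 days from ICU admission for length of stay". For the therapy durations the 30 days run from the start of the therapy.
- **Reason given:** "Treating death as a competing event rather than censoring avoids the bias whereby early deaths masquerade as short, favorable stays".
- **Fallback if proportional hazards fails:** "where violated, effects are reported as time‐varying or summarized as restricted‐mean‐survival‐time differences".

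Section 4.2 (Secondary Estimands) defines the first outcome by its exit time: "ICU length of stay is the time from ICU admission to ICU discharge or death". For the therapy durations it says that "they are analyzed in a time‐to‐event framework with death handled as a competing event".

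Section 5.1 treats secondary outcomes as supportive, without formal non-inferiority tests. Sections 4.4.1 and 5.9 nevertheless rely on them as safety indicators expected to worsen before mortality does.

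**The concern.** A restricted mean survival time is the area under a single survival curve, so a decision about death has to be made before it can be computed. The plan makes that decision for the Cox model and the cumulative incidence functions, but not for the fallback. There are two ordinary choices:

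- **Death ends the stay.** This follows directly from the length-of-stay definition in Section 4.2. Every early death then lowers the mean.
- **Deaths are censored** in a Kaplan-Meier curve for live discharge or liberation. Deaths then leave the risk set. The mean does not register them, or it shortens if those who die are the patients who would have stayed longest.

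Neither choice keeps the protection that Section 5.2 gives as its reason for competing-event handling. At stake is the sign of a safety result: an intervention that caused more early deaths could be reported as having shortened ICU stay.

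**Working it through.** The plan gives no figure for these outcomes to reproduce; its 89% power concerns 30-day mortality only. The check is therefore on the behaviour of the estimator. The 30-day horizon comes from Section 5.2. All hazards below are assumptions, because the documents give none.

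**Definitions.** Let S(t) be the probability of being still in the ICU and alive at day t, F1(t) the cumulative incidence of live discharge and F2(t) that of ICU death. At every t, S + F1 + F2 = 1. Integrating to day 30:

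- A = area under S = restricted mean with death ending the stay
- B = area under the Kaplan-Meier curve for live discharge with deaths censored
- C = area under F1 = mean time since live discharge within 30 days
- D = area under F2 = restricted mean time lost to death
- A + C + D = 30, so the change in A equals −(change in C) − (change in D)

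Extra deaths raise D and lower C. A nets the two against each other, which is why its sign cannot be trusted as a safety signal. If the discharge hazard is unchanged, a higher death hazard lowers S at every t > 0, so A must fall.

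**Check 1: constant hazards, identical patients.** Discharge hazard 0.25 per day; death hazard raised from 0.03 to 0.04 per day; ICU deaths by day 30 rise from 10.7% to 13.8%.

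- A: 3.571 to 3.448, change −0.12 days (looks better)
- B: 3.998 to 3.998, change 0 (deaths invisible)
- D: 2.832 to 3.662, change +0.83 days
- C: change = 0.123 − 0.830 = −0.71 days (worse)

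With the death hazard doubled to 0.06, A changes by −0.35 days, B by 0 and C by −2.01 days.

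**Check 2: constant hazards, two groups.** 70% of patients have discharge hazard 0.35 and death hazard 0.005. The other 30% have discharge hazard 0.08 and a death hazard raised from 0.04 to 0.06. ICU deaths rise from 10.7% to 13.7%.

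- A: 4.403 to 4.083, change −0.32 days
- B: 5.139 to 4.982, change −0.16 days
- D: 2.457 to 3.221, change +0.76 days
- C: change = 0.320 − 0.764 = −0.44 days

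**Check 3: severity varies continuously.** Z is standard normal, the discharge hazard is 0.42·exp(−0.9Z) and the death hazard 0.02·exp(Z) per day. The control values are ICU mortality 11.9% and A = 2.49 days. Changes against control, by numerical integration:

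| Scenario | ICU mortality (points) | A (days) | B (days) | C (days) |
|---|---|---|---|---|
| Death hazard +30%, all patients | +2.1 | −0.13 | −0.07 | −0.48 |
| Death hazard +35%, only patients with Z > 0 | +2.15 | −0.14 | −0.09 | −0.48 |
| Death hazard +25%, discharge hazard −3% | +2.0 | −0.05 | +0.02 | −0.52 |

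A moves in the favourable direction in every scenario computed, including the last, where live discharge is also slower. B is favourable, unchanged or slightly unfavourable, depending on how death and discharge prognosis are linked. C, read with D, has the sign that Section 5.2 intends.

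**The case against.** The strongest reply is that Section 5.2 has already fixed the event, the competing event and the horizon before it names the fallback in one clause, and nothing says that the fallback leaves that framework. The article is condensed, and the full protocol and analysis plan are said to be deposited elsewhere. The restricted mean is one of two options, used only if proportional hazards fails. The cumulative incidence functions are reported in any case, and 30-day mortality is the primary outcome, so excess deaths would be visible beside any shorter stay. All of this limits the consequence. It does not settle the wording: the estimator named is, in its ordinary meaning, one without competing-event handling, and for length of stay the stated definition leads straight to the version that shortens with deaths.

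Some stronger readings are tempting and should be resisted:

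- *A restricted mean cannot handle competing events.* It can: areas under the cumulative incidence functions are the direct analogue. The plan simply does not specify them.
- *Any rise in deaths looks favourable whichever way death is treated.* Not with deaths censored: check 1 shows no change, and the last row of check 3 shows +0.02 days.
- *Sections 4.2 and 5.2 contradict each other outright.* They can be reconciled, since one gives the exit time and the other says which type of exit is the event. For the therapy durations Section 4.2 already states competing-event handling.
- *The area under the live-discharge curve is days alive and out of ICU.* It is not, because it goes on counting after a death on the ward or a readmission. Against the plan's baseline 30-day mortality of 18%, the assumed ICU mortality of 11.9% would leave 18 − 11.9 = 6.1% of episodes with death after ICU discharge.

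**Conclusion.** The point holds as a badly fixed fallback. Computed as its name ordinarily implies, the restricted-mean difference loses the protection against early deaths that Section 5.2 claims. For a rise of about 2 points in ICU mortality, the version with death ending the stay shortens by 0.05 to 0.14 days, while mean time since live discharge within 30 days falls by about 0.5 days. The version with deaths censored moves between −0.09 and +0.02 days in the same scenarios.

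The sizes rest on assumed hazards and would differ with real ones. If harm slowed discharge much more than in the last scenario, the first version would lengthen and no longer mislead on sign. The fall in A when only the death hazard rises does not depend on the hazards chosen.

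The reach is limited to four supportive secondary outcomes, under one of two conditional fallbacks. A reader might infer that the trial's safety conclusion is compromised. The documents do not support that, because the confirmatory conclusion rests on 30-day mortality alone. The change is still worth making, because the plan uses these outcomes as early safety indicators.

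**What to change.** 1. In Section 5.2, replace the restricted-mean-survival-time difference with differences in 30-day restricted mean time by cause, taken from the cumulative incidence functions already planned. Report the area under the live-discharge (or liberation) curve together with the restricted mean time lost to death before that event. Use the same covariate and calendar-period adjustment as the main models and allow for clustering.
2. Label the first quantity as mean time since live ICU discharge (or since liberation) within 30 days, not as days alive and out of ICU.
3. In Section 4.2, state that the length-of-stay event is live ICU discharge, with death in the ICU as the competing event, to match Section 5.2.

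The cost is a change of wording and slightly more analysis code. No new data are needed, and the primary analysis and the power calculation are untouched. Section 2.5 says that all versions were finalized before outcome data were extracted or examined, so the change remains prespecified if it is made before extraction.

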### Primary Analysis—Mortality (Non‐Inferiority)

5.2

The primary analysis fits a generalized linear mixed‐effects model for 30‐day mortality with a binomial distribution and logit link. The model includes a fixed effect for treatment condition (intervention versus control), fixed effects for calendar time modeled as categorical monthly periods, fixed‐effect adjustment for the prespecified baseline covariates (SAPS 3 score, age, sex, admission type [emergency vs. planned], and ICU category [SIR Levels 1–3]), and a random intercept for cluster, implying an exchangeable within‐cluster correlation structure. Sensitivity analyses will explore alternative correlation structures, including a random cluster‐by‐period effect allowing the within‐period correlation to exceed the between‐period correlation. Because a minority of patients contribute more than one care episode, the model also includes a random intercept for patient nested within cluster. A sensitivity analysis restricted to each patient's first ICU admission during the study period will be reported.

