### Process Measures

5.3

Testing intensity is analyzed, not solely as a fidelity check but as a prespecified outcome. For each targeted category—ABG samples, venous laboratory tests, and chest radiographs—counts per patient‐day are analyzed in a mixed‐effects negative binomial model with a log link, an offset for observed patient‐days, a random intercept for cluster, and fixed effects for calendar period and treatment condition, specified analogously to the primary analysis. Effects are reported as incidence rate ratios with 95% CIs, separately by category and pooled across the three. Because these counts are ascertained from 5‐day monitoring windows at baseline and at 1 and 3 months after transition rather than continuously, the estimates describe testing intensity during sampled windows and are reported as such. Importantly, where high‐resolution electronic health record data are available, a supporting analysis using continuous data across the full study period is reported for those clusters and its agreement with the sampled estimates described. Departmental orders for vacutainer tubes and blood‐gas syringes are reported at cluster‐period level as a third, independent indicator of testing volume.

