Several limitations warrant consideration. Secular trends may confound intervention effects, although calendar time is modeled explicitly; registry data may not capture all relevant confounders; local implementation may vary between sites; and knowledge of the intervention could influence practice during control periods. As a single‐country study, the results may not fully generalize to healthcare systems with different practice patterns, culture, or resources.

Beyond patient safety and resource use, the trial will quantify the environmental impact of reducing low‐value testing, contributing to an emerging evidence base that links CW to healthcare sustainability [26, 40]. The trial does not undertake a formal health‐economic evaluation, and we make no claim about monetary savings. Most of the short‐run cost of a blood gas, a laboratory panel or a chest radiograph is staff time and installed capacity, both fixed over the horizon of this trial; reduced test volume does not become reduced expenditure unless that capacity is redeployed, and internal cross‐charging between clinical and service departments can offset an apparent saving within the same system. Reductions in testing are therefore reported in natural units and should not be read as realized savings. The environmental outcome is less exposed to this argument, since avoided consumables, reagents, and their transport are variable inputs whose emissions are avoided directly, and it is for this reason that CO_2_e rather than cost is reported as the efficiency‐side outcome. If non‐inferiority is demonstrated, the results will support evidence‐based de‐implementation of low‐value ICU diagnostics, and the design may serve as a model for similar evaluations in other settings and clinical areas.

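### As worded, the Cox models for length of stay and therapy durations carry baseline covariates and a cluster frailty but no named calendar-period effect, so time trends could enter the treatment hazard ratio

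*Protocol article*

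**What the plan says.** Section 5.2 builds the primary mortality model from separately listed parts: treatment condition; "fixed effects for calendar time modeled as categorical monthly periods"; the "prespecified baseline covariates (SAPS 3 score, age, sex, admission type" and ICU category; and random intercepts for cluster and for patient within cluster.

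Later in the same section, length of stay and the three therapy durations are given cause-specific Cox models with a gamma "frailty to account for clustering". Time runs from ICU admission or from the start of the therapy. The only statement on adjustment is "Models are adjusted for the same covariates as the primary analysis". Calendar period is not named.

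The neighbouring models are worded differently. Unplanned readmission gets a logistic mixed-"effects model specified analogously to the primary analysis". The testing-intensity model in section 5.3 names "fixed effects for calendar period and treatment condition".

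Two general statements bear on the point. Section 5.1 says that mixed-effects models will deal with clustering and temporal trends. The Discussion concedes that secular trends may confound the effect, "although calendar time is modeled explicitly". Section 5.1 also makes the secondary outcomes supportive: estimates with 95% confidence intervals and no formal non-inferiority test.

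**The concern.** In a stepped wedge, every cluster's intervention time follows its control time. A model without a calendar term therefore cannot separate the intervention from anything else that changed over the 13 months.

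Nothing else in the Cox specification fills that gap. The baseline hazard describes time since admission or since therapy start, not calendar month. The frailty absorbs stable differences between units, not a trend within them. Section 5.4, whose heading covers temporal effects, lists cluster random effects and correlation structures but no time term.

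Four of the secondary safety outcomes are affected. Section 4.4.1 offers the more sensitive safety outcomes as one ground for accepting a 3-percentage-point mortality margin. A background shortening of stay could offset a real delay in discharge or liberation and look like safety; the opposite drift could look like harm.

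**Working it through.** **The plan's own figure.** The document gives no power or precision figure for these four models. Its only power figure, 89%, is for mortality. A closed-form stepped-wedge calculation with period effects (37 clusters, 13 periods, 47 per cell, ICC 0.009, one-sided 0.025, cluster autocorrelation 1) gives 0.908 to 0.945 depending on layout and variance convention. Without period effects it gives above 0.998. Figure 1 is not shown, so 89% is neither confirmed nor refuted, but it fits a model with period effects far better than one without.

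**Step 1: separation in time.** Take a cluster that switches at the start of month s, with months 1 to 13.
- Mean control month = s/2.
- Mean intervention month = (s + 13)/2.
- Difference = 13/2 = 6.5 months, whatever s is.

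This does not depend on the roll-out layout. With a log-linear trend of b per month in the hazard of live discharge and no period term, the treatment log-HR is shifted by about 6.5b.

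**Step 2: size of the shift.** The drift sizes are assumptions; the document gives none. Let D be the total drift from month 1 to month 13, which is 12 steps, so shift = 6.5 × ln(1 + D)/12. In one simulation the standard error of the log-HR for length of stay is about 0.016 without period terms and 0.025 with them. The chance that the 95% CI excludes HR 1 under a true null is then P(|Z + shift/0.016| > 1.96).

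| Drift D | Shift | Apparent HR | Approximate false exclusion |
|---|---|---|---|
| 3% | 0.0160 | 1.016 | 17% |
| 5% | 0.0264 | 1.027 | 38% |
| 10% | 0.0516 | 1.053 | 90% |

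**Step 3: simulation for length of stay, no true effect.** Both runs use 36 clusters, 13 months, switches in months 2 to 11, death as a competing event, censoring at 30 days and a piecewise or constant-hazard Poisson equivalent of the Cox model.
- Run A (48 episodes per cluster-month, discharge hazard 1/3 and death hazard 1/30 per day, cluster SD 0.3, 200 replicates): without period terms, false exclusion is 21%, 39% and 91% for drifts of 3%, 5% and 10%. It is 34% and 79% for seasonal amplitudes of 3% and 5%.
- Run B (22,428 episodes, mean stay about 3 days, 90% live discharge, frailty SD 0.2, 300 replicates): without period terms, it is 4% with no trend, 18% at 0.25% per month (about 3% over the trial), 53% at 0.5% and 97% at 1%. It is 67% for a ±5% seasonal cycle.
- With monthly effects, both runs stay at 3% to 6% throughout.

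**Step 4: masking.** An HR below 1 means slower live discharge. With a true HR of 0.95 and D = 10%, 0.95 × exp(0.0516) = 1.00. Run A gives 1.00 and detects harm in 4% of replicates. With period terms it gives 0.95 and detects harm in 55%; the approximation ln(0.95)/0.025 = −2.05 gives 54%. Run B at 1% per month gives 1.013 without and 0.949 with period terms, the latter excluding 1 in 53%.

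**Step 5: therapies used in fewer episodes.** Run B at 1% per month, with no true effect and no period terms, gives false exclusion of 71% if 40% of episodes contribute and 19% if 10% do. The shift is about the same (HR 1.067 and 1.06); only the precision falls. The shares are assumptions.

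**The case against.** The strongest reply is that the Cox paragraph is shorthand. It does not name the treatment term either, and that term is obviously meant, so silence on period is not evidence of exclusion. Section 5.1 and the Discussion promise that time is modelled, and section 5.5 adds alternative time-trend specifications without limiting them to one outcome. Fuller versions of the protocol and plan are said to be deposited with the registration and are not shown here.

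Much of this stands. A reader might infer that the investigators chose to leave calendar time out, so that these models test for any change over the 13 months. The document does not support that: it nowhere excludes calendar time, and the general statements point to an intention to include it. The error rates also depend on a drift that is assumed, and the simulations contain no patient covariates. Adjustment for SAPS 3, age and admission type could absorb part of a seasonal change in case mix.

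What does not stand is that the wording is harmless. Section 5.2 separates model from covariates when it describes the per-protocol analysis. It lists months outside the baseline covariates, and it uses a broader phrase for readmission in the sentence that follows the Cox adjustment. Section 5.3 both names period and says "fixed effects for calendar period and treatment condition, specified analogously to the primary analysis". Only the Cox models are said to inherit covariates alone. The article describes itself as both protocol and analysis plan, and it fixes frailty distribution, time origins, censoring and proportional-hazards checks for these models. An analyst following the text could reasonably fit them without months.

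**Conclusion.** The point holds as a defect of wording with a real consequence if followed literally. On the document's own usage, the stated adjustment for the four Cox models does not include calendar period, and this sits poorly with sections 5.1 and 7.

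The 6.5-month separation is exact for any switch month, given equal weight to each month. The rates are illustrative. For length of stay, about 3% drift gives roughly 20% false exclusion of HR 1, and about 10% drift can bring a true HR of 0.95 to about 1.00. They rest on assumed drift, stay, frailty and switch months. With no drift the error is nominal, and for therapies used in few episodes the inflation is smaller although the shift remains.

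A reader might also infer that the non-inferiority conclusion is compromised. It is not: the primary model has monthly effects, and these outcomes do not gate it. Supportive status, however, does not correct a biased estimate or a misplaced interval in outcomes that are used to help justify the margin.

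**What to change.** In section 5.2, state that the cause-specific Cox models for length of stay, invasive ventilation, noninvasive ventilation and CRRT include categorical monthly calendar-period fixed effects, as in the primary model, in addition to treatment, the baseline covariates and the cluster frailty. Stratifying the baseline hazard by calendar month would serve equally well.

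The cost is one sentence and no new data. The standard error widens: for length of stay, under the simulation's assumptions, to about 0.025 from 0.016 on the log-HR, a ratio of 0.025/0.016 = 1.56. The narrower figure is valid only if nothing but the intervention changed over the 13 months. Section 2.5 says that no outcome data had been examined when the versions were finalized; if that is still so, the clarification would remain prespecified.

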### Harms

5.9

The conceivable harms of reducing routine diagnostics are delayed recognition of clinical deterioration, of laboratory derangements such as electrolyte disturbance or occult bleeding, or of mechanical complications such as pneumothorax or catheter malposition that routine imaging might otherwise detect. Because the trial is embedded in routine care and modifies testing defaults rather than introducing a therapeutic agent, harms are monitored at two levels. At the population level, the monthly safety reports track 30‐day mortality and the secondary safety outcomes by cluster and intervention status; these outcomes are deliberately chosen as sensitive upstream indicators that would deteriorate before mortality.

At the patient level, clinicians and local investigators are instructed to report any serious adverse event suspected to be related to reduced testing, in particular missed or delayed diagnoses with clinical consequences, to the principal investigator without undue delay after becoming aware of it. Causality is assessed by the independent safety review group, which reviews the case documentation and classifies events as unrelated, possibly related, or probably related to the intervention. Confirmed or suspected intervention‐related serious harms and any safety signal in the monthly reports trigger review by the safety review group, which may recommend pausing the intervention at the affected ICU or across the trial; such events are reported to the steering committee, the affected ICU, and, where required under Swedish regulations, the Swedish Ethical Review Authority. All reported events and actions taken are summarized in the trial publication. Patients are covered by the ordinary Swedish patient‐injury insurance (patientförsäkringen, LÖF).

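### Unplanned 72-h readmission codes death outside the ICU without return as a non-event, so this supportive safety outcome can look unchanged or better when deterioration after discharge is more often fatal

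*Protocol article*

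**What the plan says.** Section 4.2 (Secondary Estimands) takes the definition from the Swedish Intensive Care Registry (SIR) and describes the event "as an unplanned return to intensive care within 72 h of ICU discharge, recorded as a binary outcome per discharged episode". Section 5.2 sets the analysis set and the model: "Unplanned ICU readmission within 72 h is analyzed among live ICU discharges", with a logistic mixed-effects model specified like the primary one. Event, denominator and model are therefore all fixed in the article, and Section 2.5 says that it serves as both protocol and statistical analysis plan.

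Elsewhere the plan deals with death explicitly. For length of stay, ventilation and CRRT, Section 5.2 treats death as a competing event because this "avoids the bias whereby early deaths masquerade as short, favorable stays". For testing intensity and CO2e, Section 4.2 warns that "an intervention that increased early mortality would mechanically appear favorable on both testing intensity" and emissions, and makes those outcomes subordinate to the mortality result.

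On the role of the secondary safety outcomes, Section 5.9 (Harms) says "these outcomes are deliberately chosen as sensitive upstream indicators that would deteriorate before mortality". Section 4.4.1 uses the same argument as one of its grounds for the 3-point margin.

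**The concern.** Restricting the analysis to live discharges removes deaths in the ICU. It does not remove patients who leave alive and die outside the ICU before they can be readmitted. Under a yes/no definition these patients have not returned, so they count as non-events.

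Section 5.9 names delayed recognition of deterioration, occult bleeding and mechanical complications as the conceivable harms of less testing. If such a problem is missed at discharge, the patient may come back to the ICU or may die on the ward. A shift from the first to the second lowers the readmission rate. Readmission is the only outcome specific to the days just after ICU discharge, and the plan expects it to worsen before mortality does. An indicator that can improve as deterioration becomes more lethal does not serve that purpose when read alone.

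**Working it through.** **Step 1. Coding implied by Sections 4.2 and 5.2**

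| Course after ICU admission | In denominator? | Coded |
|---|---|---|
| Dies in the ICU | No | – |
| Discharged alive, unplanned return within 72 h (whether or not death follows) | Yes | 1 |
| Discharged alive, no return, alive at 72 h | Yes | 0 |
| Discharged alive, dies outside the ICU within 72 h without return | Yes | 0 |

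The last row is not written out in the article. It follows from the stated event and denominator, and no section makes death after discharge an event, a competing event or an exclusion for this outcome.

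**Step 2. What the coding leaves out**

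Among live discharges let r be the proportion with unplanned return and d the proportion dying within 72 h without return (0 = control, 1 = intervention). The outcome as planned compares r1 with r0. Readmission-or-death compares r1 + d1 with r0 + d0. On the risk-difference scale the two contrasts differ by exactly d1 − d0. If death without return is equally common in both conditions, nothing is lost on that scale.

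**Step 3. Illustration**

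The article gives no readmission rate, no early post-discharge death rate and no power for this outcome, so there is no figure to reproduce. All rates below are assumptions. OR = [p1/(1 − p1)] / [p0/(1 − p0)].

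| Case | Control r + d | Intervention r + d | OR, readmission | OR, readmission or death |
|---|---|---|---|---|
| a | 3.0% + 0.5% | 3.0% + 1.0% | 1.00 | (0.040/0.960)/(0.035/0.965) = 1.15 |
| b | 3.0% + 0.5% | 2.5% + 1.5% | (0.025/0.975)/(0.030/0.970) = 0.83 | 1.15 |
| c | 3.0% + 1.0% | 2.0% + 2.0% | (0.020/0.980)/(0.030/0.970) = 0.66 | 1.00 |

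With control readmission at 4% and otherwise similar shifts, the ranges are 0.74 to 1.00 for readmission and 1.00 to 1.12 for the composite. In case c the composite is flat although deaths double, so the components have to be shown as well.

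**Step 4. Would the primary outcome show the same deaths?**

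Assume that 88% of episodes end in live discharge and that all the extra deaths fall within 30 days of admission. The shift in 30-day mortality per episode is then 0.88 × 0.5 = 0.44 points (case a) or 0.88 × 1.0 = 0.88 points (cases b and c). The live-discharge share is not in the article. With 18% mortality at 30 days it should be about 82% or more, which would give at least 0.41 and 0.82 points.

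For the precision of the primary estimate, take the stated 89% power, the 3-point margin, one-sided 0.025 and a true difference of zero: SE ≈ 3 / (1.960 + 1.227) = 0.94 points. A direct stepped-wedge (Hussey–Hughes) calculation from the inputs in Section 4.4.2 gives 0.88 to 0.95 points, depending on the mortality used for the variance and on 37 or 36 clusters.

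The shifts are therefore about 0.44/0.94 = 0.5 and 0.88/0.94 = 0.9 standard errors, and well below 3 points. The primary outcome counts these deaths but would not reliably flag a rise of this size.

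**The case against.** The other side has real weight.

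- **The deaths are not lost to the trial.** The primary endpoint runs to 30 days after ICU admission whatever the place of death. It misses only patients who die within 72 h of discharge but after day 30, that is, after a stay of more than about 27 days (30 − 3). A reader might infer that the trial cannot see early ward deaths; Section 4.1 rules that out.
- **The monthly reports show both sides.** Under Section 5.8 the safety review group sees unblinded 30-day mortality beside the secondary outcomes, by cluster and condition, with quantitative mortality triggers. Section 5.9 adds reporting of suspected missed or delayed diagnoses. A reader might infer that the reports share the defect as a whole; only their readmission line does. The limit found in Step 4 is one of precision.
- **No rule turns fewer readmissions into a claim.** Section 5.1 makes secondary outcomes supportive, without formal non-inferiority testing. The Discussion says that a point estimate of excess mortality would not support de-implementation even if the margin were met.
- **The size cannot be read from levels.** One could divide assumed ward deaths by assumed readmissions and get a striking percentage. That would not measure bias, which needs a difference in d between conditions. Cases a to c require d to double or triple, and an apparent improvement also needs readmissions to fall. Nothing in the article makes this pattern likely.
- **The definition is the registry's own.** This is a good reason to keep it, but no reason to leave it unaccompanied.

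These points limit the weight of the concern. They do not answer why the plan protects its other death-sensitive outcomes and not this one.

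**Conclusion.** The point holds as a weakness in one supportive safety outcome. As defined, unplanned 72-h readmission can look unchanged or improved if deterioration after discharge becomes more often fatal, and the plan gives it none of the protection it gives the durations, testing intensity and CO2e. The consequence is a possible misreading of that outcome. The primary analysis and the trial's overall view of mortality are not affected.

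The direction of the distortion is possible, not certain, and its size is unknown. The odds ratios above rest on assumed rates and on early death without return rising under the intervention. If that risk is the same in both conditions, the readmission comparison is essentially sound. The change is still worth making, because the secondary outcomes are cited as sensitive indicators in support of the margin.

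**What to change.** Keep the SIR readmission definition as it stands. Beside it, prespecify the composite of unplanned ICU readmission or death within 72 h of live ICU discharge, analyzed in the same mixed model. Report readmission alone and death without readmission as components. Show the same three lines in the monthly safety reports. State that the readmission result is to be read together with the death component.

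No new data are needed: Section 5.11.1 already lists discharge time, time of death and precisely timed mortality in the registry extract. The change should be made before outcome data are extracted, while it can still be called prespecified.

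Costs:

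- Section 6.2 classes changes to outcomes or the analysis plan as substantive. An ethics submission, a new protocol version, a registry update and notice to the units and the safety review group are therefore required.
- Expected palliative deaths will enter the composite. Care limitations are in the extract, so a descriptive split can show how many. It should not be used to exclude patients from the main comparison, because such decisions may be made after exposure in an open-label trial and could bring in selection of their own.
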